### Interim analyses {21b}

The sponsor will set up a trial DSMB that will receive the quarterly safety update reports and analyze them accordingly for risks and benefits throughout the trial. In accordance with the statistical analysis plan, we will provide interim analysis to detect early signals of success or failure in the clinical trial. The study composes of a low-risk digital interventional trial; therefore, no formal interim efficacy analysis with predefined statistical stopping boundaries is planned. However, safety and trial conduct will be reviewed regularly. According to the DSMB’s safety reports, internal and external monitoring, and audits, there might be protocol modifications, temporary suspension, or early termination in the event of relevant safety concerns, unacceptable adverse event patterns, or major concerns regarding trial feasibility or integrity. Stopping rules were predefined within the ethics application.

### Methods for additional analyses (e.g., subgroup analyses) {20b}

Subgroups will be analyzed according to risk grouping in both groups, and compliance levels comparing the intervention and the control group based on the PROM analysis. Multivariable analysis with baseline risk factors (modifiable in both groups for later application), adjusting for levels of health literacy, risk grouping, and operations, will be performed. Significance levels of 0.05 will be assumed as clinically meaningful. A two-sided test will be applied. Center and subgroup effects will be interpreted with respect to multiplicity.

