### Outcomes {12}

#### Descriptive measures, survival analyses, and cost analyses

Primary outcome: occurrence of any postoperative complication within 90 days after surgery according to the Clavien–Dindo classification (grades I–V).

Secondary outcomes: 1-year overall survival, 6-min walking distance, QLQ-C30 quality of life score, adherence and compliance, device failures, length of stay, days on ICU/IMC, readmission rates, hospital costs.

There will be an intention to treat analysis of all included patients fulfilling the in- and exclusion criteria. Data will undergo descriptive evaluation and assessment for normal distribution utilizing the Kolmogorov–Smirnov test with Lilliefors correction. Results will be presented as median or mean with standard deviation and interquartile ranges, and/or odds ratios with 95% confidence intervals, where applicable. Survival data will be computed as the time interval from the date of surgery to the date of death, or until censoring if patients are alive at their last visit/contact.

An intention-to-treat analysis will encompass all enrolled patients meeting the predetermined inclusion and exclusion criteria. Additionally, a per-protocol analysis will be conducted.

Compliance analysis in the intervention group includes the analysis of the number of exercises performed and the exercising within the predefined thresholds. We do expect a total of 191 6-MWTs delivering 65,000 pulse points and approximately 53 Mio. pulse points from 191 patients performing 10 exercises of 47 min each during the program that will define compliance as outlined in the following. Compliance of patients in the intervention group will be categorized according to the app algorithm (green: >75% of exercises performed and >75% of all measured values are green or yellow, yellow: 50–75% of exercises performed and 50–75% of all measured values are green or yellow, red: <50% of exercises performed and <50% of all measured values are green or yellow). Comparative compliance in the control group and the intervention group will be based on a descriptive comparison of the weekly safety calls in each group during the interventional phase as PROM analysis.

Surgical procedures and indications will be categorized based on OPS and ICD-10 codes. Subgroup analyses will be conducted using chi-square testing, *T*-testing, Kaplan–Meier survival analysis, and multivariate regression analysis.

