## Statistical methods

### Statistical methods for primary and secondary outcomes {20a}

Data will be analyzed using IBM SPSS (version 29 or more current version, if applicable). Surgical procedures and indications will be categorized based on OPS and ICD-10 codes. Subgroup analyses will be conducted using chi-square testing, *T*-testing, Kaplan–Meier survival analysis, and multivariate regression analysis. The center will be included as a stratification variable. Data will be descriptively evaluated and tested for normal distribution with the Kolmogorov–Smirnov test with Lilliefors correction. Data will be expressed as median or means with standard deviation and interquartile and/or odds ratios with 95% confidence intervals where appropriate. Survival data will be calculated as time intervals from the date of their death to the date of operation, respectively be censored, if they are alive at their last visit/contact. Subgroup analyses will be conducted for predefined categories including cancer versus non-cancer surgery, abdominal versus non-abdominal procedures, and higher-risk versus lower-risk patients. Surgical category will additionally be included as a covariate in multivariable analyses to account for potential heterogeneity in baseline risk. The primary analysis will follow the intention-to-treat principle. Multivariable regression models will be used to assess treatment effects while adjusting for study center and relevant baseline characteristics. Where appropriate, mixed-effects regression models including study center as a random effect will be applied to account for the multicenter study design.

Costs will be derived from data recorded in the electronic case report form (eCRF). Costs for a day on ICU are 1500€/day, for a day on the IMC 1000€, and on general ward 500€. The DRG generated by each case will be subtracted from the sum on each treatment unit and the final sums compared between the arms. This is a two-sided approach using *T*-testing of two independent groups and a *p *value < 0.05 is regarded clinically significant.

The 95% confidence interval of the fixed effect size will be used to assess whether the treatment difference reaches the minimally clinically important difference.

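### Comparing the arms within compliance levels is not a randomised comparison and can be biased, and p < 0.05 should not be read as clinical relevance

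*Protocol article*

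**What the plan says.** All references are to the protocol article.

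- **Additional analyses {20b}.** Subgroups are formed by risk grouping and by "compliance levels comparing the intervention and the control group based on the PROM analysis". The same paragraph adds "Significance levels of 0.05 will be assumed as clinically meaningful", "A two-sided test will be applied" and "Center and subgroup effects will be interpreted with respect to multiplicity".
- **Outcomes {12}.** "Compliance of patients in the intervention group will be categorized according to the app algorithm", with green, yellow and red tiers built from sessions performed and measured values in range. For the two arms together, the plan is a "descriptive comparison of the weekly safety calls in each group during the interventional phase as PROM analysis".
- **Choice of comparators {6b}.** The control app is a digital textbook. Its data stay on the patient's phone and are not read out.
- **Statistical methods {20a}.** The primary analysis is by intention to treat. The paragraph on costs treats a t-test p value below 0.05 as clinically significant. The same section ends by saying that the 95% confidence interval will be compared with the minimally clinically important difference.

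**The concern.** Randomisation makes the arms comparable as whole groups. It does not make those who complied in one arm comparable with those who complied in the other. Fitter and more motivated patients are likely both to comply more and to have fewer complications. If that selection acts differently in the two arms, a difference in complications among compliers can appear without any effect of the app.

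Different selection is plausible here. An intervention patient complies by completing 47-minute interval sessions within heart-rate limits. A control patient has only reading material. Section {20b} does not say how patient-reported data from the calls become a compliance level with one meaning in both arms.

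The significance wording adds to the risk. Any such difference with p < 0.05 would be labelled clinically meaningful by the plan itself.

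**Working it through.** **1. The plan's own figure.** The article gives no power or sample size for the subgroup analyses. Its primary calculation (60% against 45%, 80% power, two-sided 0.05) reproduces and supplies the group size used below:

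n = [1.960·√(2·0.525·0.475) + 0.842·√(0.60·0.40 + 0.45·0.55)]² / 0.15² = (1.384 + 0.588)² / 0.0225 ≈ 173 per arm.

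**2. Size of the bias with no treatment effect.** The documents do not link compliance to prognosis, so the following is assumed. Fitness u is standard normal. Complication risk has logit 1.1·ln(1.5) − 0.8u, which gives 59.6% overall. The compliance score is ρu + √(1−ρ²)·e, and a patient is compliant if the score lies above a cut that fixes the proportion compliant. The rate among compliers is the mean of risk(u)·P(compliant | u), divided by P(compliant).

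| Intervention: ρ, % compliant | Control: ρ, % compliant | Complications in compliers, intervention / control | Spurious benefit (points) |
|---|---|---|---|
| 0.5, 50% | 0.5, 50% | 52.8% / 52.8% | 0 |
| 0.5, 50% | 0.3, 50% | 52.8% / 55.6% | 2.7 |
| 0.5, 50% | 0.5, 80% | 52.8% / 56.8% | 3.9 |
| 0.5, 40% | 0.5, 80% | 51.3% / 56.8% | 5.4 |
| 0.5, 50% | 0, any | 52.8% / 59.6% | 6.8 |

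Differences are taken before rounding. The bias vanishes when both the dependence on prognosis and the proportion compliant are equal in the two arms. Its direction is not fixed: exchanging the arms in the fourth row gives −5.4 points, so the app would look harmful.

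**3. False-positive rate.** This uses a second assumed model with 173 per arm: logit of complication = 0.45 + 0.8U, and logit of compliance = a − bU, where U is poor prognosis.

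| b, intervention / control | % compliant, intervention / control | Spurious benefit (points) | Chance of p < 0.05 |
|---|---|---|---|
| 1 / 1 | 58 / 58 | 0 | 5% |
| 0.5 / 0 | 59 / 82 | 3.2 | 8% |
| 1 / 0 | 58 / 60 | 5.8 | 13% |
| 1 / 0.3 | 50 / 81 | 6.1 | 15% |
| 1 / 0 | 50 / 90 | 7.1 | 19% |

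For the last row, SE = √(0.527·0.473/86.5 + 0.597·0.403/155.9) = 0.0665. Then 0.071/0.0665 = 1.07, and Φ(1.07 − 1.96) + Φ(−1.07 − 1.96) ≈ 0.19.

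**4. Significance is not relevance.** Take the pooled rate of 0.525 implied by the design. The smallest observed difference with p < 0.05 is 1.96·√(2·0.525·0.475/173) = 10.5 points with 173 per arm. In a half-size subgroup of 86 per arm it is 1.96·√(2·0.525·0.475/86) = 14.9 points. A 12-point difference would thus be clinically meaningful in the whole trial and not in half of it, although the benefit per patient is the same. In {20a} the phrase is attached to a cost difference in euros, where clinical significance has no meaning.

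**5. The two sections side by side.** Section {12} makes the between-arm compliance comparison descriptive. Section {20b} lists compliance level as a subgroup factor, next to risk grouping, under a two-sided 0.05 test. Both cannot govern the same analysis.

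**The case against.** **Compliance is measured differently in each arm.** A reader might infer this from the app tiers. The documents do not support it: the tiers apply within the intervention arm only, and "Comparative compliance in the control group and the intervention group will be based on a descriptive comparison of the weekly safety calls in each group". The instrument is common to both arms. What remains is that the behaviour complied with differs.

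**Spurious effects are certain.** A reader might infer this too. They are not: the bias is zero when dependence on prognosis and proportions compliant are both equal. The 6.8-point figure needs control compliance to be unrelated to prognosis, which is an extreme case.

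**Baseline subgroups are tested without interactions or regard to multiplicity.** It is tempting to read "Subgroup analyses will be conducted using chi-square testing" this way, and to add that six separate tests would carry a 26% error rate if independent. The same sentence goes on to list multivariate regression, which can carry interaction terms. Section {20b} says subgroup effects will be read with multiplicity in mind, and the detail may stand in the analysis plan, which is not shown. Neither is raised as a finding.

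**The sentence may only mean that compliance itself is compared between arms.** That reading is possible and would agree with {12}. However, the sentence is about forming subgroups, and a test level follows it, so it needs rewording either way.

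**The significance wording is only a loose name for alpha.** It is softened by the confidence-interval rule in {20a}. That rule is sound, but it gives the plan two competing standards of clinical relevance.

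**Conclusion.** The point holds in a limited form. As written, {20b} plans a comparison of the arms within levels of a post-randomisation variable that does not mean the same thing in each arm. That comparison is not protected by randomisation.

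With no treatment effect, the illustrative bias among compliers is 0 to about 7 percentage points in size, against a planned difference of 15. The false-positive rate is 5% to 19%. These figures rest on assumed links between prognosis and compliance and on assumed proportions compliant. They show the possible scale and do not forecast this trial.

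Equating p < 0.05 with clinical meaning is wrong in both places where it occurs.

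The primary intention-to-treat analysis is unaffected. So are subgroups fixed at baseline, such as cancer or type of surgery. The change should be made, but it concerns additional analyses only.

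**What to change.** 1. In {20b}, remove the between-arm comparison of outcomes within compliance levels. Keep the comparison of weekly calls descriptive, as {12} has it, and make the two sections agree.
2. Report outcome by green, yellow and red tier within the intervention arm, descriptively, with a note that the tiers are self-selected.
3. If an effect in compliers is wanted, define compliance by a threshold of sessions performed and estimate a complier average causal effect with randomisation as the instrument. State the exclusion restriction: assignment affects complications only through reaching that threshold. This needs argument here, because sessions below the threshold may also help, and the intervention includes medical guidance and a reassessment that informs the decision to operate.
4. Delete the two phrases in {20b} and {20a} that give p < 0.05 a clinical meaning. Judge relevance by the 95% confidence interval against the minimally clinically important difference, as {20a} already says.

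**Cost:** wording in the protocol and analysis plan, and one further model if step 3 is taken. The downside of step 3 is precision. If controls have no access to the programme, the estimate is roughly the intention-to-treat difference divided by the proportion compliant. At the design rates the intention-to-treat half-width is 1.96·√(0.4875/173) = 10.4 points; with an assumed 50% compliant it becomes 10.4/0.5 = 20.8 points.

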### Methods in analysis to handle protocol non-adherence and any statistical methods to handle missing data {20c}

The primary outcome will be assessed using an intention-to-treat analysis. Missing data will be reduced to a minimum by using the appropriate measures described above. Patients whose data are missing will be treated in accordance with the intention to treat principle. As the app does not allow to proceed when critical data is missing, the probability of this event is very low.

In general, it is strictly forbidden to not adhere to the clinical trial protocol outlined in the protocol. Deviations from the original statistical analysis plan can be recommendations from the DSMB or the regulatory authorities. Potential reasons can be justifiable in case patients need to be protected from potential harm in emergency situations. These situations will be documented and immediately reported to the independent review board and to the competent authority in analogy with the SAE reporting procedures. In addition, a risk-benefit evaluation will be made for those events and for the whole study cohort based on DSMB recommendations. Based on the conclusion, an amendment will be prepared, the study will be carried on, or the study will be stopped. Preventing actions include a dedicated and structured onboarding for all investigators involved. This will be documented on trial logs and stored in the ISF and TMF. Study procedures will be supported by clear checklists and supporting material for the investigators.

### Plans to give access to the full protocol, participant-level data, and statistical code {31c}

The results of the study are going to be published in a peer-reviewed journal; the data will be anonymized. The datasets used and/or analyzed during the current study can be made available by the corresponding author upon reasonable request.

## Oversight and monitoring

### Composition of the coordinating center and trial steering committee {5d}

Direct access will be granted to authorized representatives from the sponsor, the funding source, the monitors, Capreolos GmbH Knowledge and Quality, Safety and Risk Management Department, the host institution, and the regulatory authorities to permit trial-related monitoring, audits, and inspections.

Principal investigator: takes supervision of the trial and medical responsibility of the patients. The PI oversees day-to-day safety of the trial. Study coordinator: trial registration, coordinates study, visits, and annual safety reports. Data manager: organizes data capture, safeguards, quality, and data. Study physician: identifies potential recruits, takes informed consent, and ensures follow-up according to protocol. The study team meets online weekly. All parties at a center enter data into the eCRF. The coordinating center will ensure safety and data quality as well as the monitor at each site. The coordinating center is responsible for the overall conduct of the trial, including study coordination, data management, and safety reporting. The principal investigator provides overall scientific leadership and clinical oversight. The Project Management Group manages the day-to-day operational aspects of the study, including recruitment, monitoring of protocol adherence, and coordination between participating centers. The group meets weekly to review study progress.

Safety oversight is provided by the Data Safety Monitoring Board (DSMB), which reviews quarterly safety reports and provides recommendations regarding trial continuation and safety monitoring.

### Composition of the data monitoring committee, its role and reporting structure {21a}

The sponsor will set up a trial DSMB that will receive the quarterly safety update reports and analyze them accordingly for risks and benefits throughout the trial. In accordance with the statistical analysis plan, we will provide interim analysis to detect early signals of success or failure in the clinical trial.

### Adverse event reporting and harms {22}

#### Adverse events

All adverse events (AEs), adverse device effects (ADEs), serious adverse events (SAEs), and serious adverse device effects (SADEs) occurring during the prehabilitation or subsequent follow-ups will be documented in the electronic case report form (eCRF). An AE is characterized as any undesirable sign, symptom, or disease temporally associated with the application of the device, without necessitating a causal relationship. If a potential causal relationship with the device is conceivable, the AE is classified as an ADE. For all AEs and ADEs, the duration, consequences, and assessment of their relationship to the device will be recorded. AEs or ADEs resulting in life-threatening illness, injury, extended hospitalization, permanent disability, necessitating medical or surgical intervention, or death will be designated as SAEs or SADEs. They will be promptly reported to the sponsor, legal representative, and manufacturer in accordance with the regulatory obligations of the Medical Device Regulation (MDR) and the Medical Device Law Implementation Act (MPDG). Appropriate follow-up actions will be undertaken as required.

The reporting of SAEs and device deficiencies will be carried out in accordance with the Regulation (EU) 2017/745 (MDR) from May 26, 2021, in conjunction with the Medical Device Law Implementing Act (“Medizinprodukterecht-Durchführungsgesetz,” MPDG) for all clinical investigations that must be applied for or notified to the federal higher authority (“Bundesoberbehörde”). For all reportable events according to Article 80 MDR or § 64 paragraph 1 MPDG which indicate an imminent risk of death, serious injury, or serious illness and that requires prompt remedial action for other patients/subjects, users, or other persons or a new finding to it: immediately, but not later than 2 calendar days after awareness by the sponsor of a new reportable event or of new information in relation with an already reported event. This includes events that are of a significant and unexpected nature such that they become alarming as a potential public health hazard. It also includes the possibility of multiple deaths occurring at short intervals.

For SAEs or device deficiencies (DD) from German trial sites, the SAE/DD individual notification form of the BfArM will be used and sent to [name]. The sponsor will use the individual SAE report form of the BfArM. In addition, a quarterly summary of the SAE assessment will be performed using the Evaluation form and Annex 3.1 complication rates provided by the BfArM. This includes all reportable SAEs/DDs and in addition, SAEs and DDs that are included in endpoints according to the CIP (Clinical Investigation Plan). The data will be presented in comparison to scientific data from literature or other sources such as the risk analysis for all serious complications that may be related to the investigational medical device, including adverse events as a complication rate analysis. All reports will be sent to [contact]. All required procedures can be assessed in German and English language under https://www.bfarm.de/EN/Medical-devices/Applications-and-reports/SAE-report/Clinical-investigation/_node.html and will be implemented for the LUMOS trial in the SOPs for vigilance reporting by the sponsor. Reporting will be performed once every 3 months starting from the first patient being included in the clinical investigation. The following data will be provided to the competent authorities and the IRB will be informed about the regular safety reporting.

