### Objectives {7}

#### Primary endpoints

The primary objective of this study is to analyze the safety and efficacy of The Prehab App before major surgical procedures. We hypothesize that the rate of postoperative morbidity can be reduced from 60 to 45%. The primary endpoint is the occurrence of any postoperative complication within 90 days after surgery according to the Clavien–Dindo classification (grades I–V).

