## Interventions

### Explanation for the choice of comparators {6b}

The comparator used is the digitized informational app (Ready4Op). Ready4Op version 1 is a classic digital textbook without any interventional approaches to the patient. There is a basic demographic survey of height, weight, BMI, diet preferences, and fitness level of each patient before prompted to the content area which triggers individualization of the content. The content consists of 9 categories of which the 6 freely available consist of the prehab-specific content. In more than 50 subchapters, the patients receive valuable evidence-based information about the perioperative phase and can use the digital textbook as a knowledge base. There is no exchange or storage of data on a server, the demographics remain on the individual smartphone. There will be no direct readout. To better understand what the patients gained from the application, a set of standard PROMs will be documented to compare the results to the interventional group described above. The choice of comparator is the minimum recommended information patients should receive before major surgery. Experience and data show that this information often comes much too short and therefore is more than standard in an average preoperative preparation. The resource-sparing information on perioperative options to improve the individual situation before major surgeries is standard of care and does not deviate from common practice.

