### Criteria for discontinuing or modifying allocated interventions {11b}

Patients can leave the study at any time for any reason if they wish to do so without any consequences.

In case too much data is missing (e.g., missing baseline or all of the follow-up patient-reported outcome measures (PROMs), study visits), the patient will be replaced by a new patient. Early termination or temporary suspension may be recommended exclusively by the DSMB or sponsor following DSMB recommendation in case of unexpected serious safety concerns, unacceptable adverse event patterns, major protocol violations compromising participant safety, or regulatory authority requests such as ethics committee or the BfArM.

Termination criteria: unexpected safety concerns such as a significant increase in frequency or severity of serious adverse events related to the intervention, an unacceptable benefit-risk ratio therefore indication of potential risks of the intervention outweighing its anticipated benefits, a regulatory or ethical requirement due to regulatory, ethical or legal concerns, major protocol violations or GCP violations that compromise participant safety, data integrity or scientific validity, insufficient recruitment or feasibility despite corrective measurements, rendering completion of the study within the planned timeframe scientifically or operationally unfeasible, poor intervention adherence that prevents meaningful evaluation of the primary endpoint despite corrective actions, data integrity concerns, funding or logistical concerns preventing continuation of the study.

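### Adverse events are defined by use of a device that only one arm receives, so AE and SAE counts before surgery are not comparable between the arms

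*Protocol article*

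**What the plan says.** Objectives {7} puts safety alongside efficacy: "The primary objective of this study is to analyze the safety and efficacy of The Prehab App before major surgical procedures".

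The section on adverse events ({22}) sets the rule for what is counted: "An AE is characterized as any undesirable sign, symptom, or disease temporally associated with the application of the device". The rule drops causality but keeps a link in time to use of the device. An AE with a conceivable causal link to the device becomes an ADE, and AEs or ADEs with serious consequences become SAEs or SADEs. The same section says events during prehabilitation and later follow-up go into the eCRF, and it names no arm.

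The device is The Prehab App, described in Intervention description {11a} as class IIa medical software. The control arm does not receive it. Of the control app, the comparator section {6b} says: "Ready4Op version 1 is a classic digital textbook without any interventional approaches to the patient".

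Statistical methods {20a} promises a summary of all AEs and SAEs, with SAEs presented descriptively.

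**The concern.** In a randomised trial, an AE comparison is only as good as the sameness of recording in the two arms. Here the definition depends on an exposure that differs by arm. A control patient's event before surgery has no device use to be associated with, while the same event in an intervention patient does.

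The app prescribes interval exercise to patients awaiting major surgery, so the weeks before surgery are when harm from exercise would appear. If control events in that period go unrecorded, the trial cannot separate the background of falls, arrhythmias, infections and neoadjuvant toxicity from the effect of the programme. Counts would tend to show an excess in the app arm produced by the definition, or a mixture that depends on how each of the 6 centres reads the text. An analysis plan cannot recover events that were never entered.

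**Working it through.** The plan states no AE or SAE rate, so there is no figure of its own to reproduce on this point. The check sets the sections side by side and then shows how large the effect could be under stated assumptions.

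**Step 1: who is exposed.** Trial design {8} gives the intervention arm The Prehab App plus Ready4Op and the control arm Ready4Op only, 1:1. With 382 patients, 382 / 2 = 191 control patients never use the device.

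**Step 2: what the definition captures.** An AE needs a link in time to device use. SAEs are built from AEs and ADEs, so an event that fails the AE definition cannot become an SAE.

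**Step 3: when exposure occurs, and what else covers that time.** The programme runs for 3 to 6 weeks and ends before surgery.

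| Source of harm data | Time covered | Arms | Covers pre-operative AEs alike in both arms? |
|---|---|---|---|
| Clavien–Dindo I–V endpoint | surgery to day 90 | both | no, starts at surgery |
| Overall survival | counted from surgery | both | no, a death before surgery has no start date |
| Length of stay, ICU/IMC days, readmission | surgical stay and after | both | no |
| AE assessments, days 7 and 90 | after surgery | both | no |
| Weekly safety calls (Outcomes {12}) | before surgery | both | contact exists, but the stated use is a compliance comparison through PROMs |
| Exercise-symptom PROMs and the in-app safety check (Intervention description {11a}) | before surgery | intervention only | no, detection is more intensive in one arm |

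No stated outcome compares harm between arms on a common definition while the device is in use.

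**Step 4: possible size.** Assume the true pre-operative event rate p is the same in both arms, every event is recorded in the app arm, and a fraction f of events is recorded in the control arm. The expected apparent difference is

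p − f·p = p(1 − f),

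which runs from 0 (f = 1, every site reads the text broadly) to p (f = 0, literal reading). For comparison, the 95% half-width of a fully recorded difference with 191 per arm is 1.96 × √(2p(1 − p)/191). The two are equal at f = 1 − half-width/p.

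| Assumed p | Artefact, f = 1 to f = 0 (points) | 95% half-width (points) | f at which artefact equals half-width |
|---|---|---|---|
| 5% | 0 to 5 | 1.96 × √(0.095/191) = 4.4 | 1 − 4.37/5 = 0.13 |
| 10% | 0 to 10 | 1.96 × √(0.18/191) = 6.0 | 1 − 6.02/10 = 0.40 |
| 20% | 0 to 20 | 1.96 × √(0.32/191) = 8.0 | 1 − 8.02/20 = 0.60 |

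On the literal reading the artefact exceeds the random error at each assumed rate. With like recording, the same 382 patients would give an informative comparison. The rates are assumptions, not figures from the protocol.

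**The case against.** The strongest reply is that the protocol does collect harm in both arms. The sentence on recording names no arm, the day 7 and day 90 assessments apply to patients generally, weekly safety calls reach each group, and the primary endpoint is itself a randomised comparison of postoperative harm by intention to treat. All of this stands. A reader might infer that the trial has no usable safety comparison at all; the documents do not support that. It also stands that sites may read the definition broadly, so the exclusion of all 191 control patients follows from the literal wording and is not established practice.

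Two further inferences should be resisted.

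- The adverse events section says "The data will be presented in comparison to scientific data from literature or other sources such as the risk analysis". A reader might take this to mean that literature replaces the control arm. It belongs to the quarterly summary on the authority's forms and is limited to serious complications possibly related to the device. Control patients cannot supply such a rate, and nothing says this is the trial's own safety analysis. Nor does the section give a benchmark; the 60% elsewhere is the all-grade morbidity assumed for the sample size.
- The termination criteria include "a significant increase in frequency or severity of serious adverse events related to the intervention". A reader might object that no concurrent reference is named. The criterion concerns related events, and relationship to the device is recorded for every AE, so this is not a contradiction.

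Finally, the layout of safety tables and of reports to the DSMB may well sit in the full investigation plan or the SAP, and its absence here is no fault. That defence does not reach the definition itself, which this document states.

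**Conclusion.** The point holds for the period before surgery. As worded, the definition gives the two arms different rules for what counts as an AE or SAE during the only weeks of device exposure, which weakens the safety part of the primary objective. Postoperative safety comparisons are unaffected.

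The size depends on how sites apply the text. If they apply it literally, half of the randomised patients fall outside the definition before surgery and the apparent excess in the app arm equals the whole background rate. If every site records control events anyway, the excess from this cause is nil. The conclusion assumes that the device means The Prehab App; Ready4Op is nowhere described as a medical device. The sample size and the primary efficacy analysis do not change. This should be corrected, and soon, because Trial status says recruitment began in December 2025 and events not recorded at the time are hard to recover.

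**What to change.** In the adverse events section ({22}), define an AE as any untoward medical occurrence in any randomised patient of either arm, from randomisation onward, whether or not related to a device. State that it is recorded in the same way in both arms at the weekly safety calls and the postoperative follow-ups already planned. Keep relationship to the app as a separate field, so that ADEs and SADEs remain identifiable for authority reporting. In Statistical methods {20a}, say that the descriptive AE and SAE summary is shown by randomised arm, with events before surgery separated from those after.

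The cost is a wording amendment and some extra AE entry for control patients at contacts they already have.
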